### Trial registration

The trial is registered with ClinicalTrials.gov, number NCT02773966.

### Discontinuation of the trial

#### Individual withdrawal

Treatment of the patient must be discontinued if one or more of the following criteria apply:revocation of the patient’s declaration of informed consentlack of compliancediscontinuation of the therapy for other reasons deemed necessary by the responsible physician (e.g. unfavorable intraoperative geometry)Grade IV skin toxicity, i.e. skin necrosis that require surgical interventionGrade IV bone toxicity, i.e. aseptic bone necrosis that require surgical interventionGrade IV nervous system toxicity, i.e. paresis

When therapy is discontinued, the reasons for discontinuing patient participation in the study must be listed in the patient’s file.

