### Screening and randomization

After informed consent, all patients will be screened for inclusion and exclusion criteria and obtain a patient ID. A baseline visit will then be performed, which includes the assessment of the KPS and VAS scores, comorbidities and medication, a gross neurological exam, the documentation of the underlying primary cancer and the completion of the QoL questionnaires to obtain baselines. If not performed before, a CT or MRI scan of the spine will have to be performed. After fulfilment of all inclusion criteria and in the absence of exclusion criteria, patients will then be allocated into any of the two arms by block randomization (block sizes of 2 or 4 and stratification by institute). Patients randomized into Arm A will undergo Kypho-IORT, patients randomized into Arm B will undergo standard EBRT (10 × 3 Gy or 1 × 8 Gy).

The intervention (Arm A or B) should begin within a time frame of 14 days after randomization.

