### Statistical considerations

#### Trial sample size

This study is designed to test if the analgesic efficiency of Kypho-IORT is superior to standard-of-care EBRT in patients with painful vertebral metastases by comparing percentages of patients with a pain reduction of at least 3 points on VAS at defined points in time (day 1, week 2 and 6 after start of treatment).

Assuming a pain reduction of VAS-3 points at day one (first day after Kypho-IORT, one day after the first EBRT) for 40% of the patients after Kypho-IORT vs 5% of the patients after EBRT under standard pain medication (no change of the pretherapeutic pain medication 12 h after Kypho-IORT or 24 h after the first EBRT), the study will require 22 patients in each arm in order to have a two-sided alpha of 0.05 and a power of 0.817. Including a dropout rate of 20% at least 54 patients have to be recruited. The effect size was estimated on the basis of the results of the preceded phase I/II trial [11] and the results of RTOG 9714 [3].

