#### Data analysis

Data will be analysed on an intention to treat basis. All variables will be described by descriptive statistics (frequencies, means and standard deviation, medians and minimum, maximum, depending on data distribution). The Chi-square test or Fisher’s exact test will be used for categorical data. For continuous data, parametric or non-parametric mean comparison tests will be used. The Kaplan-Meier method with log-rank tests will be used to estimate relapse-free survival and overall survival.

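### The withdrawal section words stopped therapy as leaving the study, which sits badly with intention to treat and could lose day-1 pain scores selectively in Arm A

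*Protocol article*

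**What the plan says.** Three sections of the protocol article bear on this point.

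- *Data analysis*: "Data will be analysed on an intention to treat basis".
- *Individual withdrawal*: a list of reasons for which treatment must be stopped. It includes non-compliance and any reason "deemed necessary by the responsible physician (e.g. unfavorable intraoperative geometry"). The section then requires that, once therapy is discontinued, "the reasons for discontinuing patient participation in the study must be listed" in the patient's file.
- *Trial sample size*: the rates assumed at day 1 are "for 40% of the patients after Kypho-IORT vs 5% of the patients after EBRT under standard pain medication"; "the study will require 22 patients in each arm" "in order to have a two-sided alpha of 0.05 and a power of 0.817"; and "Including a dropout rate of 20% at least 54 patients have to be recruited".

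Timing matters too. *Screening and randomization* allows up to 14 days between randomisation and the start of treatment. *Objective and primary endpoint* counts day 1 from treatment: the day after Kypho-IORT in Arm A, and the day after radiotherapy begins in Arm B.

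**The concern.** Intention to treat needs an outcome, or a rule for its absence, for every randomised patient, including those whose treatment was aborted or who did not comply. The withdrawal section uses one term for stopping treatment and another for leaving the study as if they were the same event. A site reading it literally could close the file on a patient whose procedure was abandoned in theatre and take no pain score the next day.

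Such losses need not balance between arms. The worked example can occur only in Arm A, and it falls before the primary assessment. In Arm B the day-1 score is taken one day after the first or only session, so once radiotherapy has begun there is little room to stop it before that score is due. If aborted Arm A patients do worse than the rest, losing them raises the observed Arm A rate. An analysis plan can say how a missing score counts, but it cannot recover one that was never collected.

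**Working it through.** **1. The wording.** The list in *Individual withdrawal* concerns treatment; the sentence after it concerns participation. Nothing between them says that patients off therapy remain in follow-up. *Quality of life* shows that the authors could say so when they wished: questionnaires continue after progression. There is no matching sentence for stopped therapy.

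**2. Which reasons can act before day 1.** The intraoperative example acts before day 1 and in Arm A only. Withdrawn consent and non-compliance can act in either arm during the wait of up to 14 days. A Grade IV paresis could in principle arise by day 1. Grade IV skin or bone necrosis needing surgery would mostly come later and hardly touches the primary endpoint.

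**3. The protocol's own figures.** Normal approximation with pooled variance under the null, two-sided 0.05, n per arm:

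power = Φ{ [(pA − pB) − 1.96·√(2p̄(1 − p̄)/n)] / √([pA(1 − pA) + pB(1 − pB)]/n) }

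With pA = 0.40, pB = 0.05, p̄ = 0.225, n = 22: (0.35 − 1.96 × 0.1259)/0.1143 = 0.903, and Φ(0.903) = 0.817. The stated power reproduces. For dropout, 22 × 1.2 = 26.4, rounded up to 27 per arm, gives 54. Dividing by 0.8 instead gives 44/0.8 = 55, or 28 per arm; that difference is too small to matter here.

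**4. Possible inflation in Arm A.** If a fraction d of the arm is removed and all those removed are non-responders, the observed rate is p/(1 − d). The values of d are assumptions; the protocol gives only an overall 20% dropout.

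| Removed from Arm A | Patients of 27 | True 32% appears as |
|---|---|---|
| 5% | 1.35 | 0.32/0.95 = 33.7% |
| 10% | 2.7 | 0.32/0.90 = 35.6% |
| 20% | 5.4 | 0.32/0.80 = 40.0% |

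The 32% is 0.40 × 0.8, that is, 40% among those with an outcome and none among the 20% without. In Arm B the same 20% removal moves 4% only to 0.04/0.80 = 5%, so even equal losses widen the observed difference.

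**5. Power for all 54 randomised.** Suppose 20% of each arm lack a day-1 value and count as non-responders: 32% vs 4%, p̄ = 0.18, n = 27. Then (0.28 − 1.96 × 0.1046)/0.0974 = 0.771, and Φ(0.771) = 0.780. Comparing each method with itself:

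| Method | 22 per arm, 40% vs 5% | 27 per arm, 32% vs 4% |
|---|---|---|
| Normal approximation | 0.817 | 0.780 |
| Chi-square, exact power | 0.860 | 0.843 |
| Fisher's exact test | 0.773 | 0.674 |

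By the normal approximation at 27 per arm, a 20% loss in Arm A only (32% vs 5%) gives 0.737, and a 10% loss per arm (36% vs 4.5%) gives 0.841.

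**The case against.** The strongest reply is that the sentence is a filing duty. It asks for reasons to be recorded; it does not say that follow-up stops, that the day-1 score is skipped, or that the patient leaves the analysis. *Pain* schedules assessments with no exemption for stopped therapy, and its day 1 for Arm A is the first post-operative day, which an aborted operation also has. *Assessment of adverse events* continues enquiry to the end of the study. This stands as far as it goes: the harm depends on how sites read the sentence. It does not remove the ambiguity, because the sentence names participation and sits under a withdrawal heading.

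A reader might also infer more than the document supports:

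- *That the 20% allowance reveals a completers analysis.* It does not. Adding a dropout margin is routine in intention-to-treat trials, and no section excludes discontinued patients.
- *That the Arm A rate will be inflated by 8 points (32% to 40%).* This needs the whole 20% to be lost from Arm A and none of them to respond. Neither is documented, and a patient whose irradiation is aborted might still receive cement and improve.
- *That power falls from 0.817 to 0.67.* This sets a normal-approximation figure against Fisher's test, which gives 0.773 before any dropout.
- *That false-positive risk is badly raised.* With equal true rates of 5%, 10% or 20%, removing 20% of Arm A as non-responders moves the chi-square rejection rate from 0.023 to 0.045, 0.052 to 0.068 and 0.057 to 0.077. Removing 10% gives no increase.

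The 40% assumption is also cautious against the 70% reported for the phase I/II trial in *Discussion*. At 70%, the same dilution gives 56% vs 4%, with power above 0.99. Finally, sensitivity analyses for missing scores belong to an analysis plan that is not shown, and their absence here is no fault.

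**Conclusion.** The point holds as a conflict of wording with a real route to bias. The analysis section promises intention to treat, while the withdrawal section can be followed in a way that loses primary outcomes, and its one example concerns Arm A alone. The direction, towards Kypho-IORT, is plausible if aborted patients mostly fail to respond. The size cannot be stated because no abort rate is given; the 1.7, 3.6 and 8 points implied by 5%, 10% and 20% removal are illustrations, and the last is a worst case.

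The sample size is not in error. The stated power describes patients left after dropout. For all randomised patients, with 20% per arm counted as non-responders, it is about 0.78 on the same approximation.

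**What to change.** 1. In *Individual withdrawal*, separate the two events. Stopping study therapy does not end participation; the patient stays in follow-up, with the VAS collected at day 1 and later visits unless consent is withdrawn. The reasons for each event are recorded separately. The list of reasons for stopping therapy is not at issue and need not change.
2. In *Data analysis*, state that all randomised patients are analysed in the arm assigned, and that those without a day-1 value, including those never treated, count as non-responders. A patient with an aborted procedure who has a score is analysed on that score.
3. If power is quoted for all 54 patients under this rule, give it as about 0.78 for 20% loss per arm, beside the existing 0.817. Restoring 0.80 would take 29 per arm (58 in total) by the same formula; that is the sponsor's choice and not needed for the correction.

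The cost is a few sentences and one extra pain score for patients who would otherwise have left. The downside is a slightly less favourable observed Arm A rate and stated power.

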#### Investigator withdrawal

The steering committee is allowed to close the study ahead of schedule.

Other termination criteria include:insufficient patient recruitmentunexpectedly severe toxicities (second Grade IV toxicity within the study)unexpected findings which prevent the continuation of the study for ethical and/or medical reasons (new benefit/risk analysis)

## Discussion

Kypho-IORT is a technically feasible new treatment option that provided immediate pain relief, structural stability and excellent local tumor control without severe side effects in a phase I/II trial [11]. As the potential benefit of this one-stop-procedure is still unclear in comparison to the gold standard (usually 30 Gy in 10 fractions in European countries, 8 Gy single shot in the US), we designed the randomized trial introduced here. The primary endpoint of this trial is pain reduction immediately at day 1 after treatment (one day after Kypho-IORT or one day after the first/only session of EBRT, respectively). We believe that immediate pain control is a key expectation for the vast majority of patients that are referred to radiation oncology for palliation of pain.

EBRT is an integral part of local therapy, but, as seen in several studies pain control is achieved in weeks (or even months) [12]. In the initial phase I/II trial, 70% of patients that had a preoperative pain score of ≥3 reported a reduction of 3 or more points at the first postoperative day [11]. The trial presented here will thus now evaluate whether this procedure may prospectively be offered as an (potentially superior) alternative to standard external-beam radiotherapy.

## Abbreviations

CRF: Case report form
CT: Computer tomography
CTC: Common toxicity score
EBRT: External beam radiotherapy
GCP: Good clinical practice
ISF: Investigator study file
Kypho-IORT: kyphoplasty/vertebroplasty + intraoperative radiotherapy
MRI: Magnetic resonance tomography
NRS: Numeric rating score
SAE: Serious adverse effects
VAS: Visual analogue scale
